### Objectives

#### Primary Objective

The primary objective of the proposed RCT is to evaluate the effect of receiving 16 individual active music sessions compared with CAU in adults with a mild or moderate ID with CB on various outcome measures such as CB, well-being, depression, anxiety, self-esteem, and 4 domains of EF.

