## Methods

### Study Design

This study is an RCT with a pretest (T1), posttest (T2, 9 weeks after T1, unless the last intervention session was not yet completed; posttest was postponed by 1 or 2 weeks until the week after the final session), and follow-up assessment (T3, 8 weeks after T2), including 2 groups of individual participants (see Figure 1). Participants belonging to the music condition will receive 16 individual music sessions within 8 to 10 weeks, and participants belonging to the control condition will receive (individual) CAU. Randomization will be performed at a facility level for 3 reasons: first, to prevent possible interference between participants belonging to both groups in a facility; second, it is deemed unethical and difficult to explain to people with ID who are assessed to the control condition that they have to wait for the music sessions, whereas fellow residents already receive them; finally, it can also promote recruitment [17]. For randomization, a computerized random number generator will be used. There is no maximum number of participants per facility. Blinding is not possible because it is clear to the caregivers, participants, and research assistants which type of intervention a participant receives. The independent research assistants are also not blinded because the participants of the music intervention have to fill in an extra questionnaire at the second and third assessment.

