### Intervention

In this RCT, 2 conditions are compared: a music intervention and CAU.

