#### Music Intervention Group

The music intervention consists of 16 individual music sessions held twice a week within 8 to 10 weeks. Besides this individual music intervention, regular musical activities that participants already are involved in before the start of this study will continue, as music participation is a central theme of the Philadelphia Care Foundation. The 16 music sessions will be conducted by a music worker, who can be anyone who is able to play an instrument and is enthusiastic and capable to conduct musical sessions with a person with ID. Music workers are not music therapists because the focus is not on therapy but on a general active music intervention. Before the start of the music intervention, the facility in which it will take place will receive a box with an assortment of different kinds of musical instruments, including rhythm instruments (eg, cajon, djembe, and small percussion) and harmony and melody instruments (eg, keyboard and guitar). In general, during the sessions, the music worker adapts the genre or specific pieces of music to the wishes and preferences of the participant. The music intervention will be guided by a training manual for the music workers, in which the frequency, average time per (elements of the) session, and the content of every music session are outlined. The manual is designed based on the input of different advisory groups with professional music coaches, caregivers, and people with ID.

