In the manual, intervention procedures are specified, such as the setting, general goals, contents of the music sessions, basic principles of the intervention, and exemplifications. An outline of the music session can be seen in Table 1. Every session will be centered around a different aspect (introduction, emotions, different EF, and end performance), and in the training manual, example exercises are described focusing on every aspect. These examples are provided by advisory groups of professional music coaches and stem from different other manuals [41-43]. Each session will start with a welcome song, after which a listening exercise will take place. Then, a warm-up of the voice and body is scheduled, and subsequently, participants actively engage in music activities by singing or playing an instrument, after which a cool-down and a farewell song are performed. The manual provides a fixed frame for the intervention, but it leaves enough flexibility to tailor the intervention to the characteristics and needs of every participant. Participants will receive a diploma at the final session.

To study for exploratory purposes the impact of the music sessions’ frequency, some participants will receive extra music sessions, resulting in 24 to 27 sessions within the same time period, aiming at approximately 3 sessions a week.

**Table 1 table1:** Outline music session.

Music intervention	Time (minutes)	Attendees
Preliminary meeting	30	Music worker, participant, and caregiver
Music session 1: Welcoming or introduction 2-6: Emotions 7+10: EF^a^ (Inhibition) 8+11: EF (Cognitive flexibility) 9+12: EF (Working memory) 13-15: Working toward the end performance or song 16: End performance or song	60	Music worker and participant
Final meeting	30	Music worker, participant, and caregiver

^a^EF: executive functioning.

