### Data Analysis

Participant characteristics will be compared between the group receiving the individual music intervention and the group receiving CAU. Further analyses will be adjusted for any potential significant differences. The primary analyses will be undertaken on an intention-to-treat basis, and 2-sided tests will be applied at a 5% α level. In addition, per-protocol analyses will be conducted based on the sample of participants who adequately adhered to the intervention protocol by completing at least 12 of the 16 music sessions (ie, 75%), which is similar to 67% and 80% of 2 other intervention studies among adults with mild to moderate ID [67,68]. In addition, by setting the threshold at 12 sessions, we know for sure that all intervention participants followed at least 1 or 2 sessions with a focus on emotions and EF.

To minimize the number of analyses on outcome domains, the 4 different EF measures will be converted into *z* scores and, according to factor analysis, summed up into an EF domain if possible. Subsequently, to test differences in changes from baseline to follow-up between the 2 conditions, a linear mixed model analysis for each treatment variable will be used. Within each analysis, only time and the interaction between the treatment variable and time will be used [69], making it possible to adjust for the dependence of the repeated observations within the subjects. The effect of the intervention on the 2 follow-up measurements will be assessed. This analysis allows for participants with only a baseline measurement but with missing data at follow-up to be included. The normality of the residuals from the linear mixed model analysis will be visually inspected.

Secondary analyses will be performed as well. The effect of extra music interventions will be tested applying a Mann-Whitney *U* test for the between-group comparisons. The self-reported feelings before and after each music session will be compared using a Wilcoxon signed rank test.

Descriptive statistics will be used to summarize the quantitative data of the log reports, evaluation questionnaires, and the follow-up evaluation.

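### The intention-to-treat contrast pools 16 and 24–27 sessions, so it estimates the programme as delivered and not the stated 16-session effect; the extra-session comparison is open to confounding

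*Protocol article*

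**What the plan says.** The Primary Objective is to "evaluate the effect of receiving 16 individual active music sessions compared with CAU in adults with a mild or moderate ID with CB". The Music Intervention Group section defines the treatment in the same terms: "The music intervention consists of 16 individual music sessions held twice a week within 8 to 10 weeks". The same section then adds a second frequency. It opens "To study for exploratory purposes the impact of the music sessions’ frequency" and continues that "some participants will receive extra music sessions, resulting in 24 to 27 sessions within the same time period", at roughly three a week. It gives neither the number of these participants nor how they are chosen.

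The design has two arms. The Intervention section states: "In this RCT, 2 conditions are compared: a music intervention and CAU". Study Design randomises by facility, and Ethical Considerations describes allocation to one of two conditions while counting two or three sessions a week as the burden of the music condition.

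Data Analysis sets the primary analysis as intention-to-treat, with a linear mixed model restricted to time and the treatment-by-time interaction. The per-protocol set needs at least 12 of 16 sessions, described as 75%. Among the secondary analyses, "The effect of extra music interventions will be tested applying a Mann-Whitney" U test for between-group comparisons. The article names neither the variable to be tested nor the two groups; I read the groups as extra-session against 16-session participants within the music arm.

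**The concern.** The objective promises the effect of one defined exposure, but the arm that is analysed holds two. If extra sessions change the outcome, the treatment-by-time estimate is a weighted average of two effects. A report that follows the objective's wording would attach it to 16 sessions, and anyone planning to offer 16 sessions would then be quoting a figure from a partly more intensive programme.

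The second issue is the comparison of frequencies. The article calls the result an effect, but only music against care as usual is described as randomised. A rank test of two subsets cannot adjust for covariates, such as characteristics that differ between the subsets. It also treats participants as independent, although the sample size calculation assumes an intraclass correlation of 0.2 within facilities.

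Third, the per-protocol threshold is written for a 16-session schedule and has no stated meaning for participants on a longer one.

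**Working it through.** **1. The article's own figures.** Per-protocol share: 12/16 = 75%, as stated. Extra-session rate: 24/8 = 3 and 27/9 = 3 a week, in line with the stated rate of about three; over 10 weeks it would be 2.4 to 2.7 a week.

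**2. Per-protocol cut for the extra-session participants.** 12/24 = 50% and 12/27 = 44%. The article also justifies 12 sessions by the content that they guarantee. That guarantee comes from the order of sessions in Table 1, which covers 16 sessions only.

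**3. What the pooled contrast estimates.** Let q be the share of the music arm given extra sessions, and r the ratio of the effect of 24–27 sessions to the effect of 16. Then

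pooled effect / 16-session effect = (1 − q) + q·r = 1 + q(r − 1).

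This is 1 only if q = 0 or r = 1. The article gives neither q nor r. I assume q from 10% to 50%. For r, I take 1 (no added benefit) and, as the proportional case, 24/16 = 1.5 to 27/16 = 1.6875.

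| q | Mean planned sessions, 16 + 8q to 16 + 11q | Ratio if r = 1 | Ratio if r = 1.5 to 1.6875 |
|---|---|---|---|
| 10% | 16.8 to 17.1 | 1 | 1.05 to 1.07 |
| 25% | 18.0 to 18.75 | 1 | 1.125 to 1.17 |
| 50% | 20.0 to 21.5 | 1 | 1.25 to 1.34 |

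**4. Precision of the Mann-Whitney comparison.** The music arm has 44 participants (Results); the split is assumed. Using a normal approximation with asymptotic relative efficiency 0.955,

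power = Φ(d·√0.955 / √(1/n₁ + 1/n₂) − 1.96).

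At d = 0.5, ignoring clustering and dropout, this gives 0.15 for 4 v 40, 0.29 for 11 v 33 and 0.37 for 22 v 22. With the article's design effect, 1 + (2 − 1) × 0.2 = 1.2, the values fall to 0.13, 0.25 and 0.32.

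**5. What baseline adjustment adds.** Take 9 v 35 (about 20% of 44), d = 0.5 and an assumed baseline–outcome correlation of 0.7, again ignoring clustering:

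- Mann-Whitney on post-test scores: √(1/9 + 1/35) = 0.374; 0.5 × 0.977/0.374 = 1.307; power 0.26.
- Mann-Whitney on change scores: d becomes 0.5/√(2 × 0.3) = 0.645; power 0.39.
- Baseline-adjusted model: 0.5/(0.374 × √(1 − 0.49)) = 1.873; power 0.47.

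The gain from the model therefore depends on which variable the rank test would use.

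**The case against.** Most of the defence stands. The Abstract states its objective without a session count, and Ethical Considerations openly describes two or three sessions a week. On that reading the trial compares a music programme with care as usual, and the intention-to-treat analysis does so with randomisation intact. A reader might infer that the primary analysis is biased or invalid. The documents do not support that: the estimate is sound, and the mismatch lies between it and the 16-session wording of the objective.

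A reader might also infer that extra-session participants were hand-picked and that the frequency comparison is therefore confounded. No selection rule is given, and in a condensed article silence is not evidence of selection. Frequency could have been randomised in a document not shown. Open to confounding is as far as the text goes.

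Nor can it be said that the rank test throws away the baseline. The tested variable is not named, and with change scores most of the power gap in step 5 closes (39% against 47%, instead of 26%).

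The article labels the frequency question exploratory and the test secondary, which lowers the weight of that part. It does not reach the primary contrast or the per-protocol rule.

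On the per-protocol rule, 12 sessions can be defended as a minimum exposure whatever the schedule, and nothing shows that anyone would be misclassified. What remains is that the rule is stated for 16 sessions only.

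**Conclusion.** The point holds as a mismatch between the stated objective and the planned contrast, with a secondary weakness in the frequency comparison. The intention-to-treat contrast is a randomised comparison of a mixed-frequency programme with care as usual, and may be reported as such. It cannot be reported as the 16-session effect without assuming that nobody received extra sessions or that extra sessions add nothing, and the second of these is the question that the extra sessions were meant to explore.

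The size is not determinable from the documents. It is zero if extra sessions add nothing, and 5–34% if 10–50% of the arm received them and benefit is proportional to sessions. Neither the share nor the dose-response is documented, so the upper figures illustrate and do not estimate.

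The Mann-Whitney comparison is open to confounding, ignores facility clustering and cannot adjust for covariates. Under the assumed splits it would also have low power, about 15–37% for half a standard deviation before allowing for clustering. The per-protocol cut falls from 75% to 44–50% of the schedule for the extra-session participants. The point deserves correction before analysis but does not threaten the trial's main comparison.

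**What to change.** - Reconcile the Primary Objective, Music Intervention Group, Data Analysis and Ethical Considerations sections on the number of sessions. State how many participants were scheduled for 24–27 and how they were allocated. This takes no view on which number is right.
- Keep every music-arm participant in the intention-to-treat analysis, and report the primary contrast as the music programme as delivered: 16 sessions, with some participants at 24–27.
- Replace the Mann-Whitney test with a mixed model that has a three-level group (care as usual, 16 sessions, extra sessions) by time, and facility effects. Report the baseline-adjusted extra-session against 16-session contrast with its confidence interval, labelled exploratory and, unless frequency was in fact randomised, non-randomised.
- Report 16 sessions against care as usual only as a sensitivity analysis with the same caveat. It removes music-arm participants with no matching removal from the control arm, so randomisation does not protect it.
- State how the per-protocol rule applies to participants scheduled for 24–27 sessions.

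The article says that analysis follows acceptance of the protocol, so at that stage these are changes of wording plus one extra model. The costs are an imprecise dose contrast if few participants received extra sessions, and a weaker claim about them.

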#### CAU Group

Participants receiving CAU will function as a control group. CAU includes regular care such as assistance with acts of daily living and day care activities. CAU can include musical activities that participants already performed before the start of this study, as music is a central theme of the Philadelphia Care Foundation. However, new individual musical activities will be postponed for these participants until after the follow-up measurement. Participants receiving CAU will be offered a budget at the end of the study, which they can spend on musical activities or musical instruments to their own wishes, with the help of a musical specialist who works at the Philadelphia Care Foundation.

### Measures

All assessments (T1, T2, and T3) will take place by applying caregiver rating scales and self-report questionnaires and tests and all will be conducted in the same week. Students from several Dutch universities will work as research assistants assisting with the data collection. Research assistants receive theoretical and practical training in assessment through a training program in the test administration protocol. They will administer all irregularities and deviations from this protocol in a study log report. The research assistants will not be involved in the intervention itself. An overview of the outcome measures and the process evaluation can be seen in Table 2.

**Table 2 table2:** Overview outcome measures and process evaluation.

Assessment			Proxy or self-report							Measurement moment								
			Caregiver		Music worker		Person with ID^a^		Each music session			Baseline (T1)		Postintervention (T2)		Follow-up (T3)		After follow-up
**Outcome measures**																		
	Self-reports and tests					✓					✓		✓		✓			
	Proxy questionnaires	✓									✓		✓		✓			
**Evaluation^b^**																		
	Evaluation questionnaire music sessions			✓		✓							✓					
	Follow-up evaluation	✓				✓									✓			
	Self-report with emoticons					✓		✓										
	Log reports music sessions			✓				✓										
	Semistructured interview	✓															✓	

^a^ID: intellectual disabilities.

^b^Only in the music intervention.

### Outcome Measures

#### Challenging Behavior

The Dutch version of the Aberrant Behavior Checklist (ABC) will be used to assess CB, and the form will be filled out by a caregiver [44]. The ABC consists of 58 items, which are rated on a 4-point Likert scale, ranging from 0 (“not at all a problem”) to 3 (“the problem is severe in degree”). The sum of the questions provides a total score (range 0-174), with higher scores indicating more CB. In this study, the cluster structure as suggested by Kaat et al [45] will be used. The first cluster (28 items; α=.96, β=.57) represents behavior that is directed outward (ie, externalizing CB). The second cluster (26 items; α=.93, β=.76) represents behavior that is directed inward (ie, internalizing CB). For externalizing CB, the score ranges from 0 to 84, and for internalizing CB, the score ranges from 0 to 78. The total score on cluster 1 (ie, externalizing CB) will be used to assess externalizing CB, the total score on cluster 2 (ie, internalizing CB) will be used to assess internalizing CB, and the total score on all items of the ABC will be used to assess overall CB.

#### Well-Being

Subjective well-being will be assessed using the Dutch version of the 7-item Personal Well-being Index—Intellectual Disability (PWI-ID) [46]. An example of an item is as follows: “How happy do you feel about the things you have? Like the money you have and the things you own?” Each item is scored on a 3-point Likert scale (0=sad, 1=neither happy nor sad, and 2=happy). Three pictures of colored smileys are used to represent the 3 answers. The pretesting protocol, which screens for acquiescent responding, will not be applied, to diminish the data collection burden for participants. PWI-ID scores range from 7 to 24, with higher scores indicating a better subjective well-being. The PWI-ID seems to be an appropriate measure for people with a mild or upper moderate level of ID [47].

#### Depression and Anxiety

Symptoms of depression and anxiety will be assessed using the Depressed Mood and General Anxiety subscales from the Dutch version of the Anxiety, Depression and Mood Scale [48]. This questionnaire will be completed by the caregiver. The Depressed Mood subscale consists of 13 items, for example, “somber mood,” which are scored on a 4-point Likert scale (0=behavior has not occurred or is not a problem, 1=behavior sometimes occurs or is a slight problem, 2=behavior often occurs or is a relatively large/moderate problem, and 3=behavior occurs a lot or is a severe problem). Depression scores can range from 0 to 39. The General Anxiety subscale of 7 items, for example, “nervous or anxious,” are also scored on this 4-point Likert scale. Anxiety scores range from 0 to 21. For both subscales, a higher score indicates more symptoms. Its reliability and validity are satisfactory to good [49].

#### Self-Esteem

Self-esteem will be assessed using the 5-item Global Self-Worth subscale of the Self-Perception Profile for Adolescents [50]. In this study, the Dutch adaptation of the Self-Perception Profile for Adolescents [51] will be used, with a Cronbach α of >.70 and 1 statement per item [52]. An example of an item is “I am quite happy with myself.” Each item is scored on a 4-point Likert scale (1=completely untrue for me, 2=a little untrue for me, 3=a little true for me, and 4=completely true for me). The total score can range from 5 to 20, and a higher score indicates higher self-worth.

#### EF Tasks

##### Overview

EF will be assessed on a tablet using 3 computer-based games to assess cognitive flexibility, attention, inhibition, and working memory, which were custom-developed in earlier research and are adapted to the needs of individuals with ID, that is, fewer trials, shorter tasks, visual support during test instructions, and attractive stimuli [14,53]. After each game, the research assistant will complete 2 questions about how often the participant needed to be motivated and how often the participant was distracted during the games.

##### Cognitive Flexibility

The game to assess cognitive flexibility is based on the flanker task [54]. The principle of the flanker task is that participants have to respond to a target arrow, which is flanked by distracter arrows. In this study, this task will consist of 5 arrows per trial, with 32 random trials per condition, with 3 conditions. In the first condition, there are 5 green arrows pointing in different directions (left or right). Participants have to ignore the irrelevant stimuli and press the button in the same direction as the green arrow in the middle. In the second condition, the participants are presented with red arrows. Unlike the previous condition, participants have to press the button with the opposite direction as the arrow in the middle. In the third condition, participants are presented with alternating trials of red or green arrows and are requested to press the button with the opposite direction if the arrow in the middle is red and to press the button with the same direction if the arrow in the middle is green. All 3 conditions had a practice round before the official task. The score used to measure cognitive flexibility consists of the correct responses in the third condition (range 0-32). A higher score implies a higher degree of cognitive flexibility.

